### Study sample

#### Subject inclusion and exclusion criteria

Young refugees who fulfill the diagnosis of PTSD according to the *DSM-5* may take part in the study. In more detail, the inclusion criteria are:
Being a refugee allocated to a community close to one of the participating centers but not necessarily with a permanent permit to stayPTSD diagnosis according to CAPS-CA-5Age 10–18 yearsInformed consent obtained from participant (if participant is aged ≥ 16 years) or participant and caregiver/legal guardian (if participant is aged < 16 years)

For pragmatic reasons (availability of a sufficient number of ITAs in each language), YOURTREAT will mainly recruit young refugees from Syria, Iraq and Afghanistan, the countries, where the majority of refugees who were seeking asylum in Germany in 2015 originate from.

The following exclusion criteria will be implemented in the trial:
Acute risk of harm of self or others requiring inpatient treatmentClinical signs of acute psychotic disorderClinical signs of mental retardation which would prevent effective psychotherapyConcurrent psychotherapeutic treatmentAnxiolytic treatment with benzodiazepines as this medication is known to interfere with exposure-based psychotherapy (other medication is allowed and will be monitored)High alcohol or drug consumption (≥ 2–3 days of consumption per week) represents an exclusion criterion if participants cannot assure their preparedness and confidence to control their consumption in favor of the treatment that they would receive in the framework of the trial

## Procedures

### Recruitment and eligibility screening

All participating centers have extensive experience with the recruitment and treatment of children and adolescents, including young refugees. Participants will be recruited using established recruitment pathways of the specialized outpatient clinics of the centers.

In addition to these conventional recruitment procedures, the trial aims to introduce an innovative entryway for young refugees to psychotherapeutic treatment. In more detail, we plan to train ITAs who cover the most common languages among the current refugee communities, from the refugee and migrant community in each of the four participating. The tasks of the ITAs will be to interpret the diagnostic interviews and therapy sessions for all participants who do not speak German fluently in all study centers. Furthermore, the ITAs can additionally support the therapeutic process as well as the access to psychotherapy by accomplishing the following tasks:
Accompanying young refugees to and from the therapeutic sessionsReducing prejudices against mental health problems and psychotherapy by awareness-raising in the refugee community and de-stigmatization of mental health conditionsSupporting the recruitment procedure by approaching young refugees (e.g., in schools), by providing basic information about health and mental health, by offering a screening for mental health symptoms, including PTSD, using the Refugee Health Screener (RHS-15) [43] and the *Primary Care PTSD Screen for DSM-5* (PC-PTSD-5) [44], and by making qualified referrals of PTSD cases to the trial or to other specialists in the health care system

The involvement of ITAs in recruitment and psychotherapy will be documented in detail throughout the trial.

### Diagnostic procedures

Diagnostic interviews will be conducted by clinicians with at least a bachelor’s degree with the help of ITAs who interpret the interview. The first diagnostic interview (t_1_) will comprise the assessment of demographic information, a short medical anamnesis including addiction, traumatic and adverse event exposure by means of checklists for war and adversity exposure as well as family and intimate partner violence, and post-migration living conditions. Furthermore, the diagnosis and symptom severity of PTSD will be determined by administering the CAPS-CA-5 [33]. Since our population of young refugees has experienced multiple traumatic experiences, the CAPS-CA-5 symptoms can be answered in relation to several traumatic stressors (and not only to one index trauma). The CAPS-CA-5 will be amended by additional items assessing complex PTSD in the same response format. In order to be eligible for the trial, subjects will have to meet the diagnostic criteria of PTSD according to the *DSM-5* [6]. This structured interview will be succeeded by questionnaires assessing depressive symptoms and internalizing and externalizing symptoms (HSCL-37A) [35], suicidality (C-SSRS) [36], non-suicidal self-injury (four items from SITBI-G) [47], economic status and behavior (adapted from [46]), discrimination (ADDI) [37] and physical health (excerpts from SOMS-7; Rief and Hiller [38]). The follow-up interviews will employ the same questionnaires as detailed above. All diagnostic data will be recorded directly on Case Report Forms (CRFs) and are considered to be source data.

For young refugees who are accompanied by either one parent, both parents, or a legal guardian (who is not an institutional guardian), we aim at assessing mental health symptoms of guardians using the RHS and the PC-PTSD-5. If parents/guardians give their informed consent to participate, they will be screened for mental health symptoms by means of the RHS during each diagnostic interview of the child. Additionally, demographic data of the parents/guardians will also be assessed. Furthermore, we will assess the Parent Behavior Inventory [45] in order to investigate interrelations between parent/guardian mental health, child mental health and parental behavior.

See the SPIRIT Figure (Fig. 2) for an overview of the procedures of the clinical trial YOURTREAT including enrollment, diagnostic assessments and interventions.

**Fig. 2 Fig2:**
[figure not shown]
Displayed are the Standard Protocol Items: Recommendations for Interventional Trials (SPIRIT) for the clinical trial YOURTREAT including enrollment, diagnostic assessments and interventions. Abbreviations: *ADDI* Adolescent Discrimination Distress Index, *CAPS-CA-5* Clinician-Administered PTSD Scale for DSM-5 – Child/Adolescent Version, *C-SSRS* Columbia Suicide Severity Rating Scale, *HSCL-37a* Hopkins Symptom Checklist-37 for Refugee Adolescents, *KIDNET* Narrative Exposure Therapy for Children, *PC-PTSD-5* Primary Care Post-traumatic Stress Disorder Screen for DSM-5, *RHS-15* Refugee Health Screener-15, *(S)AE* (Serious) Adverse Event, *SITBI-G* German version of the Self-Injurious Thoughts and Behaviors Interview, *SOMS-7* Screening for Somatoform Symptoms 7, *TAU* Treatment As Usual, *WAEC* War and Adversities Exposure Checklist. **Next to established recruitment procedures of the study centers, participants can be recruited and screened by Intercultural Therapy Assistants as an entryway into the trial. **TAU: patients will be instructed to seek treatment within the general health care system. Therefore, in contrast to KIDNET, the duration of TAU cannot be specified a priori*

### Interventions

#### Narrative Exposure Therapy for Children (KIDNET)

In the trial, 11 sessions of KIDNET will be provided according to the manual [49]. During the treatment, the child, with the assistance of the therapist, constructs a chronological narrative of their whole life with a focus on the re-construction of the memory of the traumatic events. While the sessions dedicated to the narration of the client’s life are individual sessions with the client, parents or caregivers are invited to participate together with their children in three sessions which concern psychoeducation, current problems and future perspectives.

In the first session (100 min), the parent/caregiver should be present. For the trial, caregivers will be defined as the primary attachment figure. In case of unaccompanied refugee minors, this will be the caregiver who the child trusts the most. If the child or adolescent is unable to identify a single significant caregiver or reports that they does not want a caregiver to participate, this session takes place in individual format with the patient. The first session serves the goal of providing psychoeducation about PTSD and KIDNET, to motivate the caregiver for the continuous support of the treatment, to educate about the internalizing and externalizing stress reactions of the child and about adaptive responses, as well as to provide a continuous monitoring of the safety and well-being of the child throughout the trial. In the second session of KIDNET (100 min), which is conducted with the client alone, the lifeline exercise is performed in order to obtain a first overview of the survivor’s life story. A rope symbolizes the course of life, flowers symbolize positive emotionally arousing events, while stones symbolize negative experiences, including traumatic events. The therapist guides the patient to name the most important life experiences without going into detail. This is succeeded by the development of the narration of the patient’s life from birth to present which may start already in the lifeline session and is continued in the subsequent therapy sessions. While all significant events which were brought up in the lifeline exercise are mentioned in the narration, the most severe traumatic experiences are treated in detail by means of exposure therapy in the following sessions (100 min for each exposure therapy session). However, in contrast to other exposure-based treatments for PTSD which involve repeated exposure to one index trauma, a main focus of KIDNET is the chronological re-construction of autobiographical memory. Furthermore, KIDNET does not contain a variety of therapeutic components, such as relaxation training or cognitive coping, but mainly focuses on the narrative elements. Next to the sessions dedicated to the narration of the client’s life, KIDNET will comprise an additional session of 50 min together with the caregiver that can be scheduled during the course of exposure therapy according to the needs of the patient. It should give the caregiver the opportunity to ask questions regarding the general therapeutic process and to discuss implications of the therapy for daily life. Furthermore, options of how the caregiver can further support the therapeutic process can be discussed. If children or adolescents prefer to discuss everyday problems without the presence of the caregiver, this session will be scheduled with the patient alone. The process of the narration of the client’s life will be finalized by a reflection of the narration of the life story in the 10th session (100 min).

Finally, the last session of the therapy (50 min) will again include the caregiver and serve to celebrate the completion of the treatment as well as to discuss ways of how to cope with residual symptoms and how to further support the client. If desired by the client, the last session can also take place without the caregiver.

#### Treatment as usual (TAU)

Children and adolescents allocated to the TAU group will be referred to the local regular health care system for treatment. Immediately after the communication of group allocation, they will receive detailed information on how to find psychotherapeutic support in their community. For children under the age of 16 years, the psychoeducation on how to find psychotherapeutic support in the community will take place in the presence of the parent or guardian. The interventions provided to the TAU group will be assessed after each follow-up diagnostic assessment.

#### Choice of comparator

The aim of this trial is to test the efficacy of KIDNET for traumatized refugee children and adolescents in specialized outpatient clinics with the help of trained ITAs. For this purpose, it is necessary to compare KIDNET as provided in the specialized outpatient clinics with the efficacy of the treatment that would be available without this module, i.e., a TAU condition. So far, no data exists regarding the efficacy of TAU in this understudied population. Policy-makers often point at the limited evidence regarding the efficacy of trauma treatment for refugees in industrialized countries to justify the limited efforts to invest in the improvement of mental health care for refugees. By comparing a short-term, trauma-focused intervention with TAU for young refugees in Germany, the results of this trial could, therefore, inform major public-health related decisions in Germany; for example, regarding the usefulness of complementary treatment structures for refugees and the necessity of paying costs for interpreters for treatment.

### Measures against bias

#### Randomization

Subjects will be randomly allocated to the two arms of the trial using block-permuted randomization stratified by center based on computer-generated lists that will be provided by the independent statistician. Participants who fulfill the inclusion criteria, including a diagnosis of PTSD, will be immediately assigned to the interventions. Diagnosticians for the baseline diagnostic interview will receive a sequentially numbered, sealed, opaque envelope which will reveal group allocation in case the subject meets the diagnostic criteria for PTSD. The random sequence that determines treatment allocation is kept in a sequence of enumerated sealed envelopes that are provided to the centers. The envelopes will remain sealed to ensure concealment of the sequence of treatment allocations from the research team, assessors and the therapists. At the moment that a patient is assigned to the trial the single corresponding envelope is opened to reveal the allocation of the therapist. Block sizes vary randomly and will not be disclosed in order to assure concealment.

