## Methods

### Trial design

YOURTREAT is a randomized controlled, rater-blinded, two-arm, multi-center, superiority trial with a 1:1 allocation ratio to two parallel groups. Individuals who are screened eligible for the trial will participate in a comprehensive diagnostic interview (t_1_). Among other information (detailed below), this structured interview will assess the diagnosis of PTSD according to the *Diagnostic and Statistical Manual of Mental Disorders, 5th edition* (*DSM-5*). We expect that we will have to interview approximately *N* = 220 children and adolescents (*N* = 55 per site) in order to identify 80 participants (*N* = 20 per site) who fulfill the diagnostic criteria of PTSD. These PTSD patients will be immediately randomized to one of the two arms of the trial; KIDNET or TAU. For individuals included in the KIDNET group, the treatment starts within 1 month after the diagnostic interview and should be terminated at the latest 5 months after randomization. For the beginning and ending of the NET, a tolerance window of 1 week is considered acceptable. Deviations from this time window will be reported. Individuals assigned to TAU will be informed about treatment and counseling options within the local general health care system immediately after the diagnostic interview.

Six months after the diagnostic interview and the randomized group allocation, the first follow-up interview will take place (t_2_). This time point was selected in order to assure a minimum time interval of 1 month between the end of KIDNET and the first follow-up interview. In this way, the diagnostic interview which measures PTSD symptoms in the past month, will not be biased by the experience of symptoms during exposure therapy. The second follow-up interview (t_3_) is scheduled for 12 months after randomization. For the appointments of the follow-up interviews, a tolerance window of ±  2 weeks is considered acceptable. Deviations from this time window will be reported. See Fig. 1 for a schematic overview of the participant flow through the trial. The study protocol was written following the Standard Protocol Items: Recommendations for Interventional Trials (SPIRIT) Statement 2013 [32]. See Additional file 1 for the SPIRIT Checklist. The trial was registered at the German Clinical Trials Registry (Deutsches Register Klinischer Studien; DRKS) on 15 May 2019 (ID: DRKS00017222).

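### The baseline diagnostician holds the allocation envelope, and the opening rule requires neither the exclusion check nor a complete baseline battery

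*Protocol article*

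**What the plan says.** All references are to the protocol article.

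- **Who holds the envelope (Randomization).** "Diagnosticians for the baseline diagnostic interview will receive a sequentially numbered, sealed, opaque envelope". Its content is disclosed once the PTSD criteria are met: "which will reveal group allocation in case the subject meets the diagnostic criteria for PTSD".
- **Second wording of the trigger (same section).** "Participants who fulfill the inclusion criteria, including a diagnosis of PTSD, will be immediately assigned to the interventions".
- **Third wording (Trial design).** "These PTSD patients will be immediately randomized to one of the two arms of the trial".
- **Moment of opening (Randomization).** "At the moment that a patient is assigned to the trial the single corresponding envelope is opened".
- **Order of the t1 interview (Diagnostic procedures).** History and event checklists are listed first, then the CAPS-CA-5. After that: "This structured interview will be succeeded by questionnaires assessing depressive symptoms and internalizing and externalizing symptoms". The C-SSRS, the self-injury items, the economic items, the ADDI and the SOMS-7 excerpt follow in the same list.
- **Timing of secondary baselines (Secondary outcomes).** They are due before treatment. Nothing says before randomisation.
- **Exclusions (Subject inclusion and exclusion criteria).** Several need clinical judgement. High alcohol or drug use, for example, "represents an exclusion criterion if participants cannot assure their preparedness and confidence to control their consumption". The section does not say when the exclusions are to be judged or recorded.

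**The concern.** Two things should be settled before anyone at a site can see the arm: whether the patient is eligible, and what the baseline values are. The opening rule as worded secures the PTSD diagnosis and, through it, the baseline CAPS-CA-5. It does not secure the exclusions or the rest of the baseline.

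A site could follow the Randomization section to the letter by opening the envelope once the CAPS-CA-5 is scored. Two consequences would follow.

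- **Eligibility.** An exclusion recognised after opening leaves two poor choices. The patient stays in the intention-to-treat set although ineligible, or is removed after allocation, which undoes the protection of randomisation. Where the exclusion is a matter of judgement, knowing the arm can also influence the judgement. The Discussion itself names allegiance to the treatment as a possible limitation.
- **Secondary baselines.** The interviewer, and possibly the participant, could know the arm while the baseline questionnaires are answered. Those values enter the analysis of the secondary outcomes.

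**Working it through.** The plan attaches no figure to this point, and its sample size (72 required, 80 planned) does not depend on when the envelope is opened. The check is therefore a comparison of the sections.

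**Step 1. What each statement requires before allocation is revealed**

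| Statement | PTSD or inclusion criteria | Exclusions cleared | t1 battery complete |
|---|---|---|---|
| Randomization, envelope sentence | yes (PTSD) | not named | not named |
| Randomization, assignment sentence | yes (inclusion criteria) | not named | not named |
| Randomization, moment of opening | on assignment to the trial | not named | not named |
| Trial design | yes (PTSD) | not named | described after the interview, not stated as a condition |

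None of the four names the exclusions, and none makes a complete battery a condition.

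**Step 2. What can fall after the trigger.** In Diagnostic procedures, four instruments that serve as secondary outcomes follow the CAPS-CA-5: HSCL-37A, C-SSRS, ADDI and SOMS-7. The requirement that they be taken before treatment does not close the gap. Trial design lets KIDNET start up to one month after the interview, so a questionnaire answered after opening would still satisfy it.

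**Step 3. What cannot fall after the trigger.** The CAPS-CA-5 supplies the diagnosis that allows opening. Its baseline score is fixed before the arm is known under every wording above.

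**Step 4. How an exposed baseline would enter the analysis.** Data analyses treats continuous secondary outcomes like the primary one: a mixed model tested on the time by intervention interaction, with t1 among the time points. With time as a factor and complete data, the interaction at follow-up t compares changes:

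(KIDNET_t − KIDNET_1) − (TAU_t − TAU_1)

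Suppose that knowing the arm moves the mean reported baseline by b_K in KIDNET and b_T in TAU. The contrast then shifts by −(b_K − b_T). The shift is zero if both arms move equally, and otherwise goes point for point into the interaction. The planned between-group comparisons at t2 and t3 contain no t1 term under the same conditions, but they are run only if the interaction is significant. For the CAPS-CA-5, b_K = b_T = 0 by Step 3. The documents give no value for b_K or b_T on the other scales.

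**Step 5. What happens to a late exclusion.** The attrition-bias paragraph and Data analyses both keep every participant as randomised. No rule is given for a patient found ineligible after the envelope is opened, so it matters that eligibility is settled first.

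**The case against.** The strongest defence is that the intended order can be read from the article. Trial design says that only people already screened as eligible enter the t1 interview, and it describes randomisation after that interview. It also has TAU participants informed directly after the interview, while the TAU section places that information directly after the arm is communicated. Together these put communication at the end of the interview. The medical history, including addiction, is listed before the CAPS-CA-5, so information on substance use may already be at hand. The SPIRIT figure and the full protocol are not shown and may state the order.

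Much of this stands, and it rules out several stronger readings that a reader might infer.

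- **That allocation comes before the eligibility decision by design, or that the envelope is opened mid-interview.** No section says so. The exclusions have no stated time, early or late.
- **That suicide risk is assessed too late because the C-SSRS follows the CAPS-CA-5.** The C-SSRS is listed as a secondary outcome. Nothing makes it the tool for the acute-risk exclusion.
- **That envelopes are used up by interviews ending without randomisation, which would break the blocks.** Opening is tied to assignment to the trial ("At the moment that a patient is assigned to the trial the single corresponding envelope is opened"), and no text says that an unopened envelope is discarded.
- **That the next allocation can be foreseen.** The envelopes are opaque and numbered, the lists come from an independent statistician, and the block sizes vary and are undisclosed. Follow-up raters are blinded.

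What the defence does not supply is a rule. When the family is told is not the same as when the diagnostician may open the envelope. The only screening tools the recruitment section names are the RHS-15 and PC-PTSD-5, which are symptom screens, and no section says that the exclusions are cleared at that stage. A sealed envelope prevents prediction. It does not prevent its holder from making a discretionary exclusion after opening it.

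**Conclusion.** The concern holds in a limited form. The opening rule is loosely worded: the diagnostician who rates PTSD holds the envelope, and the stated trigger leaves out both the exclusions and completion of t1. The exposure is confined to judgement-based exclusions made after the arm is known and to the baseline values of four secondary instruments. The baseline CAPS-CA-5 and the sample size are unaffected.

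The size of any bias cannot be derived from the documents, which give neither the frequency of late exclusions nor the effect of a known arm on questionnaire answers. If sites in practice open the envelope only at the end of the interview with every criterion settled, the bias is nil and only the text needs correcting.

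The conclusion assumes that the diagnostician also rules on the exclusions. The article names nobody else for that decision but does not say so outright. It also assumes that no fuller document already fixes the order. The change is worth making because it is cheap and protects concealment, eligibility decisions and secondary baselines together.

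**What to change.** Reconcile Trial design, Diagnostic procedures, the TAU section and Randomization so that they state one sequence:

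1. The whole t1 battery is completed.
2. Every inclusion and exclusion criterion is recorded on a dated eligibility form.
3. Existing staff other than the diagnostician, for example the Data Management Team or the independent statistician, release the next allocation in that site's sequence.
4. A number is used only for a patient confirmed eligible on that form.

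Baseline diagnosticians would then no longer hold envelopes. The Secondary outcomes section should say that t1 values are taken before randomisation, not only before treatment.

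The cost is protocol wording and one message per randomised patient, 80 in all, to staff already in the trial. The drawback is a short delay, from minutes to perhaps a day, before the family learns the arm. The wording on immediate assignment and on immediate information for TAU participants would have to allow for it. The sample size and the analysis model do not change.
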